| Secondary outcomes                                        | 
 
- Clinical score (neurological deficit) using the NIHSS at 7 days and 3
 
- Functional scale (modified Rankin score) at 7 days
 
- Autonomy scale (Barthel index) at 7 days and 3 months
 
- Percentage of patients back home at 7 days and 3 months
 
- Length of stay
 
- Prevalence of swallowing disturbances, pneumopathy, urinary tract infection, bladder catheterization, deep vein thrombosis during
 
                                                                                                                                                                                                                                                                                                                                                                                                                                                                                                                                                                                                                                                                                                                                                                                                                                                                                                                                                                                                                                                                                                                                                                                                                                                                                                                                                                                                                  |

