### **EOOBM may decrease the rate of complications linked to prolonged immobility**

Complications associated with immobility are: deep vein thrombosis, pneumopathy, urinary tract infections, constipation and pressure sores.  In the setting of stroke, a study led in Denmark showed that, over 11757 patients, 2969 (25.3%) presented at least one complication during hospitalization: Urinary tract infections (15.5%), pneumopathy (8%), and constipation (7%). 

In this study, early mobilization within the first 24 hours after stroke onset significantly decreased the complication rate. These results were confirmed by several pilot studies comparing the « usual » procedure to early out of bed activity. Indeed, mobilized patients showed less pneumopathy, urinary tract infection and fall. 

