#### **2.2.2. Secondary outcomes**

Clinical score (neurological deficit) using the NIHSS at 7 days and 3

Functional scale (modified Rankin score) at 7 days

Autonomy scale (Barthel score) at 7 days and 3 months

Percentage of patients back home at 7 days and 3 months

Length of stay

Prevalence of swallowing disturbances, pneumopathy, urinary tract infection, bladder catheterization, deep vein thrombosis during hospitalization

Side effects of upright positioning in the two groups= tolerance of early sitting (prevalence of side effects)

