### 7 day visit (or before exiting the hospital if before D7)

Will be documented:

- Clinical data

- NIHSS
- Rankin score
- Barthel score

Exit of the hospital:

- Cause of the cerebral infarction, if available
- Internal carotid artery status (ultra sounds)
- Date
- Orientation of the patient (back home, rehabilitation, ...)
- Immobility related complications during hospitalization

3 month visit

Will be documented:

- Clinical data
  - NIHSS
  - Rankin score
  - Barthel score
- Cause of the cerebral infarction
- Presence/Absence of post stroke fatigue
- Synthesis about complications that occurred during the hospital stay

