#### Secondary outcome

- Clinical score (neurological deficit) based on the NIHSS at 7 days and 3 months: comparison of the mean scores between the two groups using a Student's test.
- Functional scale (Rankin score) at 7 days: comparison of the proportions of patients with a score [0-2] by a Chi square test.
- Autonomy scale (Barthel index) at 7 days and 3 months: comparison of the proportions of patients with a score < 60 (dependent) between the 2 groups using a Chi square or a Fisher test
- Length of stay: comparison of the means between the two groups using a Student's test
- Percentage of patient back home before 7 days or 3 months: Chi square test or Fisher test.
- Side effects associated with sitting in the two groups (tolerance of upright positioning in the early versus progressive arms) : description of the side effect in the 2 groups and comparison of the most frequent (>5%) by a Chi square test or a Fisher test.

- Prevalence of swallowing disturbance, pneumopathy, acute urinary retention, bladder catheterization, deep vein thrombosis during hospitalization: comparison between the two groups using a Chi square test or a Fisher test.
- Prevalence of post stroke fatigue: comparison between the two groups using a Chi square test or a Fisher test.

A multivariate logistic regression model will be used in a second step to adjust on age and former (before the qualifying event) Rankin score.

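### Urinary tract infection is a listed outcome but acute urinary retention is what gets compared, and 3-month home status has no listed data source for patients discharged elsewhere

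*Protocol*

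**What the plan says.** **Urinary item.** Protocol section 2.2.2 defines the complication outcome as "Prevalence of swallowing disturbances, pneumopathy, urinary tract infection, bladder catheterization, deep vein thrombosis during hospitalization". The abstract's secondary outcomes row has the same items: "Prevalence of swallowing disturbances, pneumopathy, urinary tract infection, bladder catheterization, deep vein thrombosis during" (the sentence runs on over the page break). Section 6.2.1, under the secondary outcomes, plans this instead: "Prevalence of swallowing disturbance, pneumopathy, acute urinary retention, bladder catheterization, deep vein thrombosis during hospitalization", compared between the arms by a chi-square or Fisher test. The abstract's statistical analyses row carries the same list as section 6.2.1.

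**Return home.** Section 2.2.2 and the abstract define the outcome as "Percentage of patients back home at 7 days and 3 months". Section 6.2.1 and the abstract's analysis row plan a chi-square or Fisher test of the percentage home *before* 7 days or 3 months. In section 5.2, living situation is documented at inclusion, and the hospital-exit items include the date and "Orientation of the patient (back home, rehabilitation" and so on. The 3-month visit lists NIHSS, Rankin, Barthel, cause of the infarction, fatigue and a summary of in-hospital complications. It lists no residence item.

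**The concern.** A secondary outcome should appear under the same name where it is defined, where it is collected and where it is tested. Here two of them do not.

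For the urinary item, a statistician following section 6.2.1 literally would test a variable the protocol never declared as an outcome. The declared one would get no between-group test, although it is the complication that the protocol's rationale reports as most frequent. One stated secondary aim (section 2.2.1) is to show fewer immobility complications with early sitting, so this component bears directly on that aim.

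For return home, the test at 3 months needs to know where each patient is living, or whether and when the patient got home. The listed items stop following location at hospital exit. The abstract also words this aim as getting home faster, which needs a date of return for patients who go home by way of another facility.

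**Working it through.** No sample-size or power arithmetic bears on this point. The check sets the protocol's lists side by side.

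**1. Urinary item, list against list**

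| Item | Outcome lists (abstract; 2.2.2) | Analysis lists (abstract; 6.2.1) |
|---|---|---|
| Swallowing disturbance | yes | yes |
| Pneumopathy | yes | yes |
| Urinary tract infection | **yes** | **no** |
| Acute urinary retention | **no** | **yes** |
| Bladder catheterisation | yes | yes |
| Deep vein thrombosis | yes | yes |

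Each list has five items. Four agree and one is swapped.

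**2. Which term the rest of the protocol supports.** Section 1.1 says: "Complications associated with immobility are: deep vein thrombosis, pneumopathy, urinary tract infections, constipation and pressure sores". Urinary tract infection is also named in the risk-benefit discussion (1.2.3) and among the expected events of the progressive arm (7.2). Acute urinary retention is in none of these places. In the cohort cited in section 1.1, at least one complication occurred in 2969/11757 = 25.3% of patients, as stated. Urinary infection is given as 15.5%, pneumopathy as 8% and constipation as 7%. Urinary infection is therefore the most frequent of the three, at 15.5/8 = 1.9 times the pneumopathy rate.

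**3. What is collected.** Section 5.2 records immobility-related complications as a class at exit. Urinary infection belongs to that class by the protocol's own account. Section 6.2.1 opens by saying that every collected parameter will be described by group. So infection would probably be collected and tabulated by arm; what it lacks is a planned comparison. Retention has a planned comparison but is named in no data-collection list.

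**4. Return home at 3 months, by patient course, using only the listed items**

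| Course | Known from listed data? |
|---|---|
| Died in hospital, or still in hospital at 3 months | Yes: not home |
| Died after discharge, before 3 months | Yes for *at* 3 months: Rankin 6, so not home |
| Discharged straight home | Yes for *before* 3 months, from exit date and destination |
| Discharged home, institutionalised later | No for *at* 3 months: looks the same as a patient still at home |
| Discharged elsewhere, alive, then home | No: no residence and no date of return |
| Discharged elsewhere, alive, never home | No: looks the same as the row above |

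The 7-day status can largely be derived from exit date and destination.

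**5. *At* against *before*.** A patient sent home in the first week and institutionalised by 3 months counts as a success under *before* and a failure under *at*. The outcome sections use one word and the analysis sections the other.

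**6. Size.** The protocol gives no expected share of patients discharged elsewhere. As a scale only: for every 10% of the 400 planned patients who leave hospital alive for another facility, 0.10 × 400 = 40 have no determinable home status at 3 months.

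**The case against.** The urinary mismatch could be one drafting or translation slip. The abstract's analysis item repeats section 6.2.1, so its second appearance is not independent evidence. Section 6.2.6 promises an analysis plan before database freeze that will detail changes to the statistical section, and the label can properly be corrected there. All of this stands, but the operative text is still wrong and needs the correction.

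On return home, section 6.1.1 promises that the electronic file will hold the data needed for the planned analyses. It points to section 7, which covers vigilance, but the intent is presumably the statistical section. The schedule table in 5.2 is plainly incomplete: it omits fatigue, and it omits cause of the infarction at 3 months, although the visit lists require both. Absence from that table therefore proves little, and section 5.3 covers only data held outside the medical file. The eCRF itself is not shown and may contain a residence field. What survives is that the detailed 3-month visit list has no such item, and a general promise supplies neither the item nor its definition. An analysis plan can correct a label; it cannot create residence data that were not collected.

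A reader might infer three stronger things that the documents do not support:

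- *That the two endpoints are not delivered.* Urinary infection would probably still be described by arm, the other four complications are tested, and 7-day home status is largely derivable.
- *That 3-month home status is unknown for everyone not discharged straight home.* Deaths and patients still in hospital can be classified.
- *That outcome switching has occurred or must follow.* A change documented before freeze that brings the test back to the listed outcome is a correction.

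**Conclusion.** Two secondary endpoints are wrong as written.

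- **Urinary tract infection** is an outcome without a planned comparison, and acute urinary retention has a planned comparison without being an outcome. One item in five is swapped. This rests on the text alone and is held with high confidence.
- **Return home at 3 months** cannot be classified from the listed data for survivors discharged to rehabilitation or another facility, or, under the *at* definition, for patients institutionalised after going home. The number affected is not given in the protocol. This part assumes that the 3-month visit list in section 5.2 reflects what is collected; a residence field in the eCRF would reduce it to a documentation gap. The difference between *at* and *before* remains either way.

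The primary endpoint, its test and the conclusion from it are unaffected. The corrections should be made because they are cheap and because missing residence data may not be recoverable once follow-up is over.

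**What to change.** 1. In section 6.2.1 and the abstract's statistical analyses row, replace acute urinary retention with urinary tract infection, so that the tested item is the listed outcome. Record the change in the analysis plan before database freeze, as section 6.2.6 provides.
2. Add two items to the existing 3-month visit in section 5.2 and to the eCRF: current residence, and date of return home.
3. Choose *at* or *before* for the home endpoint and use the same word in section 2.2.2, section 6.2.1 and both places in the abstract.

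The cost is a wording change and two fields at a visit already planned. It needs no extra visit, no extra patients and no change to the primary analysis.

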### **6.2.2. Statistical justification for the number of patients required**

In a meta-analysis of two pilot studies comparing an « early » to a « usual » mobilization procedure, Craig and coll. (9) showed that the percentage of patients with a Rankin score [0-2] was 34.7 % at 3 months in the « usual » group (n=49) versus 57.4 % in the « early » group (n=54).

In our study, we hypothesized that the functional outcome at 3 months assessed by the Rankin score will be better in the « early » group than in the « progressive » group, with a percentage of Rankin [0-2] of 35% in the « progressive » group and 50% in the « early » group. With an alpha risk of 5% and a power of 80% (bilateral), 183 patients per group are required to show a difference. Total number will then be 366 patients.

Percentage of poor tolerance during the first sitting is estimated between 5 and 10% in the 2 groups. As this may affect the Rankin score at 3 months, the number of patient to include has been increase to 400.

If the superiority of the « early » group is not statistically demonstrated, a switch to non inferiority could be undertaken. For this analysis, the non inferiority threshold is set at -5 % (maximum acceptable clinical difference). With 400 patients, non inferiority will be demonstrated if the real difference between the two groups is between 9 and 15%.

Reference: Committee for Proprietary Medical Products (CPMP). Points to consider on switching between superiority and non inferiority. 2000. European Medical Agencies (AMEA). CPMP/EWP/492/99.

The study will be undertaken in 11 centers. Each one, has the potential to recruit patients, with at least 300 cerebral infarction cases a year.

### **6.2.3. Significance**

Significance is set at 5%. If a witch to non inferiority is done, bilateral confidence interval of 95% will be built and the inferior border will be compared to the non inferiority threshold set at -5%.

#### **6.2.4. Statistical criteria to stop the study**

NA.

#### **6.2.5. Missing, unused and invalid data**

In the situation of a side effect requiring the patient to lie down immediately, or in case of patient death, the Rankin score will be set in the [3-5] interval at 3 month (penalized).

No imputation will be performed on the secondary outcome parameters.

#### **6.2.6. Management of the modifications made to the initial plan for analysis**

An analysis plan will be written before the freezing of the database and will detail the potential modifications made to the statistical section of the protocol.

#### **6.2.7. Choice of the patients to include in the analyses**

To analyze for superiority, the population will be analyzed in «intent to treat» (ITT). This population corresponds to all the patients randomized in the study.

Analysis of sensibility on the population « Per protocol » (PP) will be realized to verify the solidity of the results. This population includes patients who strictly respect inclusion and exclusion criteria, present no protocol deviation and for whom the primary outcome is available. This analysis will exclude deceased patients and the patients with a serious side effect during the first sitting process.

In the non inferiority analyses, analyses in ITT and PP have the same importance. In case of switch to non inferiority, the two analyses will be performed in parallel and the results will be considered accurate if they are the same in the two analyses, in accordance with the recommendations for non inferiority analyses "Points to consider on switching between superiority and non-inferiority" - Guideline EMEA."

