#### **6.2.8. Randomization**

The randomization list will be created by a statistician from the clinical research department of Nantes university hospital. Randomization will be performed using blocks and a ratio of 1:1.

A sealed envelop that contains the randomization # and the group affiliation will be created for each patient. These envelops will be numbered and stored in each participating center. Each time a patient is included, the investigator will take the next envelop, following the numerical order.

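### The per-protocol set drops deaths and serious first-sitting side effects, so it cannot check the ITT non-inferiority result if those events are commoner in the early arm

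*Protocol*

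**What the plan says.** Section 6.2.7 defines ITT as all randomised patients. PP contains patients who meet the entry criteria, have no protocol deviation and have a primary outcome. It then adds a further restriction: "This analysis will exclude deceased patients and the patients with a serious side effect during the first sitting process".

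The same section uses PP as the sensitivity analysis for superiority and raises its standing after a switch: "In the non inferiority analyses, analyses in ITT and PP have the same importance". The non-inferiority result is accepted only if the two analyses agree.

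Section 6.2.5 handles overlapping events differently. A patient who has to lie down at once because of a side effect is scored as a failure, and likewise "in case of patient death, the Rankin score will be set in the [3-5] interval at 3 month (penalized").

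On frequency, 6.2.2 offers only this: "Percentage of poor tolerance during the first sitting is estimated between 5 and 10% in the 2 groups". No death rate is given.

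**The concern.** Death and a serious reaction at first sitting happen after allocation and may be caused by it. Section 1.2.3 names neurological worsening as the main risk of the study, and 7.2 lists it specifically for the early arm. Removing patients because of such events leaves a comparison of those who survived and tolerated sitting, which is no longer a randomised comparison.

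PP is given weight in a non-inferiority analysis because non-adherence pulls the arms together in ITT and can make an inferior procedure look acceptable. PP can correct for that only if it still counts the harm. Here it removes patients whom 6.2.5 scores as failures. If early sitting does cause more of these events, PP becomes the more lenient of the two analyses. The superiority sensitivity analysis would then be flattered in the same way.

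**Working it through.** **Inputs from the protocol.** 6.2.2 gives a "percentage of Rankin [0-2] of 35% in the « progressive » group and 50% in the « early » group", two-sided alpha 5%, power 80%, 183 per group raised to 400 in total, and a margin of -5 points. 6.2.8 gives 1:1 allocation, so 200 per arm. 6.2.3 tests the lower limit of the two-sided 95% interval.

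**The plan's own figures.** With a mean rate of 0.425,

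n0 = [1.960 × √(2 × 0.425 × 0.575) + 0.842 × √(0.35 × 0.65 + 0.50 × 0.50)]² / 0.15² = 169.3, that is 170 per group.

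With the continuity correction, n = (n0/4) × [1 + √(1 + 4/(n0 × 0.15))]² = 182.4, that is 183, which matches the protocol. Non-inferiority power at 200 per arm is Φ((d + 0.05)/SE - 1.96): 82% at d = +9 points and 98% at +15, consistent with the range stated in 6.2.2.

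**Assumptions for the check.** Every removed patient is a failure in ITT. There are no other PP exclusions until non-adherence is added below. Agreement means that both analyses show non-inferiority. The removed shares are assumptions, varied around the protocol's 5-10%.

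**PP at the margin.** Take a true ITT difference of -5 points (35% progressive, 30% early). If shares e_p (progressive) and e_e (early) are removed, the PP rates are 0.35/(1 - e_p) and 0.30/(1 - e_e), on 200(1 - e_p) and 200(1 - e_e) patients. For 5%/10%: 0.3684 and 0.3333, d = -0.0351, SE = 0.0496, and Φ(0.0149/0.0496 - 1.96) = 4.9%. The last column is the simulated rate at which ITT and PP both pass (300,000 trials, full adherence).

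| Removed, progressive/early | PP difference (points) | PP alone passes | ITT and PP both pass |
|---|---|---|---|
| none | -5.0 | 2.5% | 2.5% |
| 5% / 5% | -5.3 | 2.2% | 2.0% |
| 10% / 10% | -5.6 | 1.9% | 1.6% |
| 5% / 10% | -3.5 | 4.9% | 2.4% |
| 5% / 15% | -1.6 | 10.1% | 2.5% |
| 10% / 20% | -1.4 | 10.1% | 2.5% |
| 10% / 5% | -7.3 | 0.8% | 0.8% |

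**An example in counts.** Suppose 70/200 progressive and 78/200 early patients succeed, with 10 and 30 removed. ITT: +4.0 points, lower limit -5.45, fails. PP: 78/170 - 70/190 = +9.0 points, lower limit -1.1, passes. The two disagree, so non-inferiority is not accepted.

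**With non-adherence.** The true rates among adherers are again 35% and 30%. A share of early patients does not adhere, has progressive-arm outcomes and is dropped from PP (400,000 simulated trials, 200 per arm). False is judged here against the -5 points among adherers; 20% non-adherence shrinks the ITT difference to 0.8 × -5 = -4 points.

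| Non-adherence; removed, progressive/early | Joint rate, PP as written | Joint rate, events kept in PP |
|---|---|---|
| 20%; 5% / 15% | 3.6% | 2.1% |
| 20%; 5% / 10% | 2.9% | 2.1% |
| 30%; 5% / 15% | 3.9% | 2.0% |

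In the first row ITT alone passes 4.0%. A PP that keeps the events brings this down to 2.1%; PP as written brings it down only to 3.6%.

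**The case against.** The strongest reply is that PP never decides alone. ITT keeps every one of these patients, with deaths and lie-down events as failures, and a favourable PP cannot rescue a failing ITT. This stands under full adherence: the joint rate never exceeds about 2.5%. A reader might take the 4.9% or 10.1% for PP alone as the trial's error rate; the agreement rule in 6.2.7 does not support that.

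A reader might also infer that this PP set always favours early sitting. The protocol does not support that either. Section 6.2.2 gives one tolerance range for both groups, under which PP is slightly stricter than ITT. Section 7.2 lists immobility complications for the progressive arm, so an excess of removed events there is possible and would reverse the bias.

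Nor is a PP more favourable than ITT in itself an error. With 35% success in the progressive arm, 5%/15% removed and equal success among those retained, ITT is -3.7 points and PP is 0, but -3.7 lies inside the margin, so a pass there is not false.

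Two further replies stand in part. Sections 6.2.5 and 6.2.7 can both be followed, since one scores events and the other defines a set; the strict inconsistency is in how the side effects are described. And a patient whose sitting was stopped may have missed the 15-minute minimum in 5.1.2, so calling such a patient non-deviant is arguable, although 5.1.2 itself foresees stopping for side effects. For deaths no such argument applies.

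**Conclusion.** The point holds in a conditional form. The exclusion selects on outcome after randomisation and removes patients whom 6.2.5 scores as failures. Its direction depends on which arm has more of the removed events: toward non-inferiority if the early arm, slightly conservative if equal, against non-inferiority if the progressive arm. The case that matters is an early-arm excess, because that is the harm a non-inferiority claim has to rule out.

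The effect on the final decision is modest. It is nil or conservative under full adherence. It appears when non-adherence dilutes ITT, which is what PP is meant to guard against: about 3.6% instead of 2.1% at 20% early-arm non-adherence and 5%/15% removed. These figures rest on assumed event splits and adherence, and on scoring every removed patient as a failure. The defect of definition does not depend on them.

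**What to change.** In 6.2.7, delete the exclusion sentence. Define PP by eligibility at entry, adherence to the allocated positioning schedule, and availability of the 3-month outcome. State that deaths stay in PP as failures, and that patients with first-sitting side effects stay in PP and are scored by the same rule as in ITT, so that no patient is a failure in one analysis and a success in the other. Say also that a sitting stopped for a side effect does not by itself count as a deviation for this purpose; otherwise the exclusion could return through the no-deviation criterion.

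Reconcile the event wording: 6.2.5 refers to side effects that make the patient lie down at once, 6.2.7 to serious ones. One definition should serve both sections.

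The cost is one paragraph of wording, settled before the database is frozen, with no extra data or patients. The PP result may look slightly less favourable.
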